### Evaluation design

2.3.

In order to evaluate the intervention, we combine a trend study consisting of a repeated retrospective cross-sectional survey (27) at four measurement time points (2020, 2021, 2022, 2023), with an accompanying process evaluation of the information campaign. The process evaluation is based on the recommendations of the British Medical Research Council for complex interventions (20). The evaluation of complex interventions faces the challenge that when outcomes are being assessed it is not always immediately determinable which elements have contributed to success or non-success in the sense of describable effects on the outcome, due to the multiplicity of different elements and their possible interactions (28). A description of the assumed mechanism of action of the intervention together with an evaluation of the implementation of the individual intervention elements (e.g., reach, dose delivered, dose received), can help to better understand which factors of the complex intervention may have affected the outcome (28). Knowledge about implementing the different modules is not only important to explain observed outcomes, however, but also with regard to the further development or adaptation of the intervention in other settings. The potential mechanism of impact for the MiMi-Reha-Kids intervention and the interaction of the different modules is shown in Figure 2.

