	Questionnaire 1 for mediators (at each individual appointment)	Dose received	Subjective evaluation of the implementation of the training date
			Recommendations of the mediators to improve training
	Questionnaire 2 for mediators (after completion)	Recruitment/reach	Sociodemographic data of the mediators
		Dose delivered	Data on attendance at the individual training dates
		Dose received	Subjective evaluation of the implementation of the entire training
			Recommendations of the mediators to improve training
Information events in the native language (Module 2)			
	Documentation sheet for mediators	Recruitment/reach	Number of participants
		Fidelity	Implementation of the module in comparison to the conceptual design (e.g., duration, contents); Feedback from mediators on implementation problems with closed and open-ended questions
		Dose delivered	Location of the information session
			Duration of the information session
			Information session language
			Sociodemographic data on the mediator performing the mediation
			Materials used
			Information on topics covered
			Subjective evaluation of implementation of the information session from the mediator’s point of view
	Questionnaire for participants in twelve languages	Recruitment/reach	Sociodemographic data of the participants
		Dose received	Subjective evaluation of implementation of the information session
Individual support for rehabilitation requests (Module 3)			
	Monitoring of the implementation	Dose delivered	Number and duration of consultations
		Recruitment/reach	Number of participants, language of consultations
	Documentation sheet for mediators	Fidelity	Implementation of the module in comparison to the conceptual design (e.g., duration, contents); Feedback on implementation problems with closed and open-ended questions
Transcultural training for professionals (Module 4)			
	Recruitment monitoring	Recruitment/reach	Number of participants
	Documentation sheet for instructors	Fidelity	Implementation of the module in comparison to the conceptual design (e.g., duration, contents); Feedback from instructors on implementation problems with closed and open-ended questions
		Dose delivered	Training duration
			Subjective evaluation of implementation of the training from the instructor’s point of view
	Questionnaire for participants of the training	Recruitment/reach	Sociodemographic data of the participants

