#### Trend study

2.5.1.

The primary outcome of the trend study on the utilization of rehabilitation is the proportion of children and adolescents with a migrant background among those undergoing rehabilitation who reside in Berlin or Hamburg. The migrant background is assessed in this study in accordance with the minimum indicator set for recording migration status (29).

We determine an individual as having a migrant background if they immigrated from another country and have at least one parent who was not born in Germany, or have two parents who immigrated and/or do not have German nationality.

This definition allows a differentiation between children with unilateral and bilateral migrant backgrounds (30). The information on the country of birth and nationality of the parents and the child required to map the migrant background is assessed through a questionnaire, and combined with data from the insured person’s account. The primary language, residence status, and duration of residence of the child and the child’s parents are also assessed.

In order to provide a description of the samples and to describe differences between children and adolescents with and without a migrant background in the samples, the health-related quality of life of the children and adolescents [KIDSCREEN-27 (31)], sociodemographic and socioeconomic information on the children and the parental home (32), perceived social support (33) and satisfaction with the rehabilitation service received will be collected through questionnaires as part of the trend study. The questionnaire data is supplemented by administrative data on medical rehabilitation (e.g., duration, and discharge diagnosis according to ICD-10) from parents’ insurance accounts. The data collected in the trend study is shown in Table 2.

**Table 2 tab2:** Data collected as part of the trend study.

Data	Source^2^	Sample 2020	Sample 2021	Sample 2022	Sample 2023
Migration history (34)		x	x	x	x
Nationality^1^	Questionnaire for parents/administrative data	x	x	x	x
Country of birth^1^	Questionnaire for parents	x	x	x	x
Primary language^1^	Questionnaire for parents	x	x	x	x
Duration of stay^1^	Questionnaire for parents	x	x	x	x
Residence status^1^	Questionnaire for parents	x	x	x	x
Socioeconomic status (31)	Questionnaire for parents	x	x	x	x
Social support (32)	Questionnaire for parents	x	x	x	x
Health-related quality of life (KIDSCREEN-27) (30)		x	x	x	x
Physical wellbeing	Questionnaire for parents/child	x	x	x	x

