#### Process evaluation

2.8.2.

Participants receive an anonymous questionnaire at the end of a session, which is completed on site and submitted to the instructors. The documentation and questionnaires for Modules 1, 3 and 4 are available in German. The questionnaires for participants in information events in their native language (Module 2) are available in twelve languages (see above), and are distributed according to the language of the participants. The instructors send the questionnaires, together with the completed documentation forms, by mail to the University of Lübeck, where all data is recorded electronically.

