### Data management

2.9.

A comprehensive data protection concept was developed in coordination with German pension insurance, which ensures data processing, the rights of the persons involved, as well as the technical and organizational measures for the secure and confidential collection, processing and storage of data. Researchers at the University of Lübeck only receive pseudonymized data from the insured persons and their children as part of the trend study. The generation of data within the process evaluation is anonymized. All questionnaire data is entered, checked and transferred to statistical software programs for further analysis. Data entry and data verification are performed by trained research assistants. Questionnaire data from the trend study is linked to administrative data from the insurance account using a pseudonym. Access to the data is limited to the authors and research assistants on the research team.

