## Conclusion

4.

The study described in this protocol will provide comprehensive data on which persons can be reached within the different modules of the multimodal information campaign and how the information campaign and its different modules are perceived by the participants. The results of the trend study will also provide information on whether the utilization of medical rehabilitation by children and adolescents with a migrant background could be increased over the intervention period at the intervention sites. Thus, possible changes in utilization can be related to the specific implementation of the modules of the information campaign. These data can help organizations and institutions to adapt or further develop the multimodal information campaign or specific modules for other regions in Germany or other countries.

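### The trend study, as listed, records no contact with the campaign, so it cannot show whether additional migrant rehabilitants were reached, or by which module

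*Protocol article*

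**What the plan says.** Section 2.5.1 of the protocol article says "The data collected in the trend study is shown in Table 2". Table 2 lists migration history (nationality, country of birth, language, length of stay, residence status), socioeconomic status, social support, KIDSCREEN-27, satisfaction, rehabilitation dates and diagnoses, each for all four samples. No row concerns contact with the campaign.

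The process evaluation is a separate data stream. Section 2.8.2: "Participants receive an anonymous questionnaire at the end of a session, which is completed on site and submitted to the instructors". Section 2.9: "The generation of data within the process evaluation is anonymized". The only linkage described is within the trend study: "Questionnaire data from the trend study is linked to administrative data from the insurance account using a pseudonym".

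The purpose of the process evaluation is set out in Section 2.3: knowing how the elements were implemented "can help to better understand which factors of the complex intervention may have affected the outcome". Section 4 goes further: "Thus, possible changes in utilization can be related to the specific implementation of the modules of the information campaign". Section 1.4 gives the aim as clarifying whether the campaign increases access and utilization, and Section 2.3 says effectiveness will be tested by the trend study. Only families in Berlin and Hamburg are surveyed, so there is no comparison region.

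**The concern.** The trend test answers one question: did the proportion of rehabilitants with a migrant background rise between rehabilitation years 2019 and 2022? The article wants a second answer as well: was the campaign, or a particular module, behind the rise? With no control region, the most direct evidence would be whether the additional families had met the campaign at all. As listed, neither data stream holds that information. The trend data have no contact item, and the process data have contact but no link to rehabilitants.

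A rise made up entirely of families who never met a mediator would look the same in these data as a rise made up entirely of families who did. A positive result could then be credited to the modules, and the campaign extended to other regions, on evidence that cannot separate the two cases.

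**Working it through.** **Passages side by side**

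- Trend study (Table 2): outcome and descriptive variables for each rehabilitant, no contact variable, pseudonym shared with the insurance account only.
- Process evaluation (Table 1, Sections 2.8.2 and 2.9): counts, durations, languages and ratings per session or participant, anonymous.
- Common variables: calendar year; city, because both streams are confined to Berlin and Hamburg; and language. Table 1 records "Information session language" for Module 2, and Section 2.5.1 says "The primary language, residence status, and duration of residence of the child and the child’s parents are also assessed".

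A comparison is thus possible only between groups (year, language, city). Modules 1 to 4 overlap in 2021 and 2022, so calendar year cannot separate them.

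**The plan's own figure**

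Inputs from Section 2.6.1: proportions 10, 11, 13 and 16%; 432 per year; 40% participation of 1,200, i.e. 0.40 × 1,200 = 480. From Section 2.10: two-sided 0.05. Cochran-Armitage test with scores x = 0, 1, 2, 3 (mean 1.5) and equal n per wave:

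- T = n·Σp(x − 1.5) = n × 0.10
- s0 = √(n × 0.125 × 0.875 × 5)
- s1 = √(n·Σp(1 − p)(x − 1.5)²) = √(n × 0.55765)
- Power = Φ((T − 1.96·s0)/s1)

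n = 432: T = 43.2, s0 = 15.37, s1 = 15.52, power 0.800 (simulation 0.802). n = 480: T = 48.0, s0 = 16.20, s1 = 16.36, power 0.840 (simulation 0.842). The 432 and the 84% both reproduce, so the primary test is not in question.

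**Scale of what cannot be seen**

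Assuming the yearly total stays at 1,200, the additional children with a migrant background are 1,200 × (0.01, 0.03, 0.06) = 12, 36 and 72 for rehabilitation years 2020, 2021 and 2022, together 120.

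- Module 3 plans 48 consultations. If all led to rehabilitation, that is 48/120 = 40% of the rise, and 48 × 0.40 = 19.2 respondents. If a quarter did (assumption), it is 12/120 = 10% and 4.8 respondents.
- Module 2 plans about 2,400 attendees, far more than 120, so the planned reach does not limit the answer: the share of the 120 with campaign contact could lie anywhere from none to all.

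**How weak the group comparison is**

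Same formula within one city. With an equal split (assumption, 240 per city and year): T = 24.0, s0 = 11.46, s1 = 11.57, power 0.55. With a one-third to two-thirds split (160 and 320): 0.40 and 0.68.

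**What an exposure-removed trend would do**

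Suppose the campaign has no effect, the proportion stays at 10% of 480 (48 children), and a share c of the migrant respondents had contact in the last wave. Removing them gives (48 − 48c)/(480 − 48c):

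| c (assumption) | Proportion left |
|---|---|
| 5% | 45.6/477.6 = 9.5% |
| 10% | 43.2/475.2 = 9.1% |
| 20% | 38.4/470.4 = 8.2% |
| 50% | 24/456 = 5.3% |

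The proportion falls although nothing happened, so the contrast measures reach and not effect.

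**The case against.** The strongest reply is that no person-level linking was ever planned. Section 4 speaks of relating changes to how the modules were implemented, Section 2.3 gives the process evaluation an explanatory role, and Section 2.10 says its data will be presented descriptively. A comparison between groups needs no shared identifier. This stands: a reader might infer that the two streams cannot be related at all, and the documents do not support that. The comparison is weak and uncontrolled, but possible.

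Second, the questionnaires are not shown and Table 2 is not itemised to the last question. Section 2.5.1 names sociodemographic information that has no row of its own. The missing row is therefore strong evidence, not proof, that contact is not asked.

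Third, a contact item would not cure the lack of a control. Everyone surveyed has already received rehabilitation, and a family that attended an event might have applied anyway. This also stands. A reader might infer that the item, or a trend calculated after removing exposed families, would settle attribution. It would not: the table above shows that such a trend falls under a campaign with no effect. In the other direction, families reached by word of mouth or through professionals trained in Module 4 could tick none.

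What the reply does not remove is that the article states its data set and then draws a conclusion about the modules that this data set does not support.

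**Conclusion.** The point holds in a limited form. As listed, the trend study cannot show whether additional rehabilitants with a migrant background were reached by the campaign, or by which module, and the sentence in Section 4 goes beyond an aggregate comparison by year, language or city. Under the plan's assumptions about 120 additional children are at issue, with a share reached that these data leave unknown. This rests on Table 2 being complete as regards contact items and, for the 120, on a constant 1,200 rehabilitants a year.

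The gap does not touch the primary outcome, the trend test or the sample size. Nor is it the reason why a causal claim is out of reach: that follows from the uncontrolled series. A contact item narrows what can be said about direct reach and does no more. It is worth doing because it is cheap and bears on the study's stated aim.

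**What to change.** 1. Add one tick-box item to the parent questionnaire in all remaining waves: attended an information event; helped by a mediator with the request; received the multilingual guide; none; don't know. The 2020 wave covers rehabilitation in 2019, before the modules began, and needs no item. The 2023 wave matters most: it covers 2022, which carries 72 of the 120 assumed additional children (60%).
2. Report, by wave, the number and share of respondents with a migrant background who had contact, descriptively, as an approximate upper bound on the part of the rise that could come from direct contact. If few or none had contact, do not attribute the rise to direct reach. If many had, this is consistent with an effect but does not prove one.
3. Do not use a trend recalculated without exposed families as a test of attribution.
4. Limit the sentence in Section 4 to an aggregate, descriptive comparison. This applies even if no remaining wave can be changed.

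Cost: one questionnaire item and a small data-protection update. Recall of contact is imperfect, indirect exposure (word of mouth, Module 4) is missed, the bound applies to respondents only, and waves already fielded stay without the item; the article says the surveys have begun but not how many remain.

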#### Process evaluation

2.5.2.

The process evaluation takes into account recommendations from Saunders et al. for developing and describing complex interventions (34). Accordingly, the components recruitment/reach, fidelity, dose delivered, and dose received will be assessed using different questionnaires and documentation forms as part of the process evaluation for the modules of the intervention (Table 1).

### Sample size

2.6.

#### Trend study

2.6.1.

A sample of 432 persons per year must be recruited in order to be able to demonstrate a change in the proportion of children and adolescents with a migrant background among the rehabilitants from 10 to 11%, 13, and 16% in the trend study [Cochran-Armitage test for trend (35)]. With a participation rate of 40% and 1,200 children and adolescents residing in Berlin or Hamburg receiving rehabilitation, power of 84% is needed to detect a significant trend. If the participation rate for persons without a migrant background is higher than for persons with a migrant background, the total sample size increases. Despite the observed reduced proportions of children and adolescents with a migrant background, the strength of the Cochran-Armitage test for trend is almost unchanged for the then-expected reduced trend.

#### Process evaluation

2.6.2.

No sample size calculation was made for the process evaluation. We intend to recruit 120 participants for mediator training (Module 1) and 2,400 participants in the information events (Module 2). We expect 48 participants for individual counseling on requests for medical rehabilitation (Module 3), and 60 participants from the health care sector in transcultural training (Module 4).

### Recruitment

2.7.

#### Trend study

2.7.1.

In the fourth quarter of 2020 to 2023, the German Pension Insurance identifies, based on administrative data, all insured persons residing in Berlin or Hamburg who have a child who received medical rehabilitation from the German Pension Insurance in the previous year (i.e., 2019, 2020, 2021, and 2022) and who was 17 years old or younger at the time of rehabilitation. These insured persons form the sample of the trend study.

#### Process evaluation

2.7.2.

People who participate in a session within the framework of the four modules during the information campaign are asked to complete questionnaires on site. Instructors document the sessions on documentation sheets.

### Data collection

2.8.

#### Trend study

2.8.1.

Trend study data will be generated through questionnaires and from administrative data from insured accounts. Insured persons identified by the German pension insurance will receive a cover letter, study information, a parent questionnaire, a child questionnaire (for the child who received medical rehabilitation), and a consent form for the use of administrative data at the beginning of the 4th quarter of 2020, 2021, 2022, and 2023. The questionnaires are pseudonymized. The questionnaires are returned to the University of Lübeck by the insured persons and electronically recorded there. The declaration of consent is sent by the insured persons to the German Pension Insurance, who send one reminder after four weeks. If consent is given, German pension insurance sends a pseudonymized data set with data from the insured persons’ accounts to the University of Lübeck, where this administrative data is linked to the questionnaire data using the pseudonym.

#### Process evaluation

2.8.2.

Participants receive an anonymous questionnaire at the end of a session, which is completed on site and submitted to the instructors. The documentation and questionnaires for Modules 1, 3 and 4 are available in German. The questionnaires for participants in information events in their native language (Module 2) are available in twelve languages (see above), and are distributed according to the language of the participants. The instructors send the questionnaires, together with the completed documentation forms, by mail to the University of Lübeck, where all data is recorded electronically.

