#### Information events in the native language (Module 2)

2.2.2.

After completing the training, the mediators inform migrants about medical rehabilitation for children and adolescents in independently conducted information events in their native language (Module 2). In addition to their training folder, the trained mediators receive other support materials, such as a multilingual guide to medical rehabilitation for children and adolescents (see Additional file 2) that can be handed out to interested parents and adolescents, and a PowerPoint presentation that they can use for the information session. Both the guide and the presentation present the contents of the training in a condensed and easy-to-understand form. In addition to a German-language version, these materials are available in Arabic, Bulgarian, English, Farsi, Italian, Kurdish, Polish, Russian, Spanish, Serbian/Croatian/Bosnian and Turkish, so that information events can be held in the native language of parents and interested parties. The information events should have a duration of about 120 min, and be carried out with about 10 participants. The information events can take place at different locations in the migrants’ social environment, for example in migrant cultural associations, but also in doctors’ offices, schools or EMC venues. The mediators are responsible for organizing the sessions themselves, but receive support from the EMC if necessary. The mediators receive a financial compensation for each information session held. Overall, it is planned that the mediators will hold a total of 240 information events by the end of 2022, thus informing around 2,400 people in Berlin and Hamburg about the possibilities of medical rehabilitation.

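### Participant rating forms in Modules 1, 2 and 4 return through the person who ran the session, which creates a risk of favourable bias in the descriptive 'dose received' results

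*Protocol article*

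**What the plan says.** Section 2.8.2 (Data collection, Process evaluation) gives two steps. First: "Participants receive an anonymous questionnaire at the end of a session, which is completed on site and submitted to the instructors". Second: "The instructors send the questionnaires, together with the completed documentation forms, by mail to the University of Lübeck". Section 2.9 (Data management) adds: "The generation of data within the process evaluation is anonymized".

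Table 1 lists a participant form with a subjective rating, under 'dose received', for Modules 1, 2 and 4. For Module 2 the item reads "Subjective evaluation of implementation of the information session". The Module 2 form, the Module 4 form and the second Module 1 form also collect sociodemographic data. Table 1 lists no participant rating form for Module 3.

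On who runs Module 2, section 2.2.2 says that "the mediators inform migrants about medical rehabilitation for children and adolescents in independently conducted information events in their native language", that events should "be carried out with about 10 participants", and that "The mediators receive a financial compensation for each information session held".

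Section 4 (Conclusion) says the study will provide data on "how the information campaign and its different modules are perceived by the participants".

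The trend study works differently. In section 2.8.1, families return their questionnaires to the university themselves.

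**The concern.** A rating handed to the person being rated invites kinder answers, and the person who posts the forms is able to read them or leave some out. Both mechanisms push the same way. The word 'anonymous' protects respondents mainly toward the university. It protects them less toward a mediator who has just spent about two hours with some ten people and then receives their forms.

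Other features of the plan add to this. Mediators are recruited for their wide networks in the community (section 2.2.1), so some attendees may know them. The same mediators offer individual help with rehabilitation requests (section 2.2.3), so an attendee may expect to need that help next. In Module 1 the training ends with an examined presentation (section 2.2.1), while trainees' ratings go back through the instructors.

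At stake is the credibility of the participants' view of the modules, which the article offers to other organisations that may adapt the campaign. The process data are only described (section 2.10), and the article states no analysis step that would correct a favourable tilt. More forms would not remove it.

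**Working it through.** The plan states no figure for this point, so there is nothing to reproduce. The check has two parts.

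**1. The route, read across sections**

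| Step | Process evaluation (2.8.2) | Trend study (2.8.1) |
|---|---|---|
| Who receives the completed form | the instructor, on site | the university |
| Who forwards it | the instructor, by post, with their own documentation | nobody in between |
| Does the form rate that intermediary's session? | yes in Modules 1, 2 and 4 (Table 1) | not applicable |

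Section 2.8.2 says only 'instructors'. Reading this as the mediators in Module 2 is an inference, but a strong one: they conduct the events and fill in the Module 2 documentation sheet (Table 1).

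**2. How large could it be? Illustration under assumptions**

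Inputs from the documents: planned participants of 120 (Module 1), 2,400 (Module 2) and 60 (Module 4), from section 2.6.2; 240 events of about 10 people, and 240 × 10 = 2,400 agrees with section 2.2.2.

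Inputs assumed, not in the documents: true favourable share p of 0.70, 0.80 or 0.90; fraction s of the remaining participants affected, of 0, 0.10 or 0.30.

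The two mechanisms need different formulas.

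- Switched answers: excess = (1 − p) × s.
- Forms not forwarded: reported share = p / (1 − (1 − p) × s), because the denominator shrinks.

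| p | s | Excess if switched (points) | Excess if withheld (points) |
|---|---|---|---|
| any | 0 | 0 | 0 |
| 0.70 | 0.10 | 3.0 | 2.2 |
| 0.70 | 0.30 | 9.0 | 6.9 |
| 0.80 | 0.10 | 2.0 | 1.6 |
| 0.80 | 0.30 | 6.0 | 5.1 |
| 0.90 | 0.10 | 1.0 | 0.9 |
| 0.90 | 0.30 | 3.0 | 2.8 |

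At p = 0.80 the reported share is 82% to 86% if answers switch, and 0.80/0.98 = 81.6% to 0.80/0.94 = 85.1% if forms are withheld.

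For scale, the 95% half-width at p = 0.80 is 1.96 × √(0.80 × 0.20 / n):

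- Module 2, n = 2,400: 1.6 points if people are treated as independent. Allowing for clustering in events of 10, multiply by √(1 + 9 × ICC). An assumed ICC of 0.05 gives 1.6 × √1.45 = 1.9; an ICC of 0.10 gives 1.6 × √1.90 = 2.2.
- Module 1, n = 120: 7.2 points.
- Module 4, n = 60: 10.1 points.

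At p = 0.80 an excess of about 2 to 6 points is therefore larger than sampling error over most of its range in Module 2, and smaller than it in Modules 1 and 4. Across the grid the one exception is Module 1 at p = 0.70 and s = 0.30 with switched answers: 9.0 points against 1.96 × √(0.70 × 0.30 / 120) = 8.2. Sampling error is only a yardstick here, since all participants are asked.

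**The case against.** The strongest reply has five parts.

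- **The article is condensed.** Section 2.9 refers to a data protection concept that covers confidential collection, and it is not shown. Envelopes may already be in use. This stands: the text does not say that forms are handed over open, and silence on envelopes is not evidence against them. It does not remove the point, because the route through the instructor is stated, and the same article states a direct route for the trend study.
- **The forms are anonymous.** This stands in part. Table 1 does not name the sociodemographic items, so recognition within a group of about ten is possible but not shown. The Module 1 form used at each appointment lists no such items.
- **Payment.** A reader might infer that mediators gain from good scores. The documents do not support that: compensation is per session held, with no stated link to ratings. It shows an interest in the programme and nothing more, and the passage concerns Module 2 only.
- **The Module 1 completion form covers the whole training.** It spans nine days led by subject-specific instructors, so whoever collects it need not be the only person rated. This stands and weakens the point for that form.
- **Missing forms can already be detected.** The Module 2 documentation sheet records the number of participants and travels with the forms, so counts can be compared now. This stands, with the limit that the attendance figure is the mediator's own. The comparison also says nothing about answers softened before hand-over.

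**Conclusion.** The point holds as a risk to the descriptive 'dose received' ratings in Modules 1, 2 and 4. The expected direction is favourable. Its size cannot be derived from the documents, and zero is not excluded; the figures above rest wholly on assumed values of p and s. The case is clearest in Module 2, where one person runs the event, collects the forms and posts them, and where the planned numbers are large enough for a shift of a few points to exceed sampling error.

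A reader might infer that the perception results are in fact biased, or that the study's effectiveness result is compromised. Neither follows. The documents show a vulnerable collection route, not its consequence. Reach, fidelity and dose delivered come largely from other items or tools and do not depend on these ratings. The primary outcome, the proportion of rehabilitants with a migrant background, comes from questionnaires returned directly to the university and from administrative data, and is unaffected. This is an inexpensive improvement to make, not an error in the analysis.

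**What to change.** Change the return step in section 2.8.2. Participants seal the anonymous form in an envelope, or drop it in a closed box, before it leaves their hands, and it is opened only at the university. The instructor or mediator may still post the package.

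For each event, report the number of forms received against the documented attendance, and note for Module 2 that attendance is the mediator's own count. Sealing is the stronger of the two measures, because it acts on softened answers as well as on selective forwarding.

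Flag forms collected before the change so that the two sets can be shown separately. If sealed return was already used, one sentence saying so settles the point. If collection has ended, state the return route as a limitation wherever the ratings are reported.

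The cost is the envelopes or boxes, a line of instruction and slightly more handling. No analysis in the trend study changes.
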